3.2 Primary endpoint/outcome

The primary outcomes are categorized as follows: (1) Outcomes directly related to the health status and condition management of the participants (e.g. weight, BMI, HbA1c, blood pressure, waist, generic health status, smoking yes/no, confidence in diabetes management and meal planning, healthy eating) and (2) Outcomes directly related to platform intervention usage:

- Number / Duration of sessions
- Number of users / average sessions per user
- New users
- Monthly Active Users / Weekly Active Users
- Specific actions:
  - # Recipes Viewed, (any indication on favourite content)
  - # Recipe Added / Saved
  - # Meal Plans created
  - # Shopping Actions
    - Carts sent online
    - Meal plans sent to cart
    - In store shopping actions - print, email, sms, app, etc.
    - Number of items shopped / value
- Platform used - app vs web app
- GA audience metrics: Demographics, Geography,
- User Retention
- Top 20 recipes (potentially)
- The average or typical meal plan including health score (potentially)

Additionally, expectations beforehand and satisfaction afterwards will be assessed. Diabetes UK will collect data regarding their traffic on the website and the amount of referrals to the online platform.

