The lead CU researchers will send an invitation email to participants to fill in the first survey (please see Attachment 1) with enclosed Participant Information (PI; please see Attachment_2) and Informed Consent Form (ICF; please see Attachment_3) explaining the project aim, related activities and burden in terms of duration. The email will contain a link to the first survey (hosted by Qualtrics; please see Attachment_4) in which both PI and ICF are embedded. Two automated reminder emails will be send by Qualtrics in cases where participants do not fill in the first survey, one after a week of non-response, and one after two weeks of non-response. All data will be deleted in case there is non-response after the three emails. If participants do not want to be contacted or receive any reminder emails they can email they would like to UNSUBSCRIBE. Each participant will be provided with a unique survey link that recognises each participant by a unique response number only. The end of the first survey will present the option if the participant is (1) willing to participate into a prize draw (using their email address) and (2) willing to participate in follow-up research so selected participants can be approached for the case studies or semi-structured online interviews. After 8 weeks of using the platform, participants will receive an invitation email (please see Attachment_5) to fill in the second survey (please see Attachment_6).

Based on platform usage data (low vs. high engagement) and provided consent at the end of the first survey, participants will be selected for further research activities which consist of case study and semi-structured online interviews. Participants selected for the case study interview will receive an invitation email (please see Attachment_7) with PI (please see Attachment_8) and ICF enclosed. Participants who are willing to participate into the case study interview will sign the ICF (please see Attachment_9) and send it back to the CU lead researcher. Participants who prefer a phone interview can indicate this in an accompanying email. The case study interview outline is presented in Attachment_10.

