**7.5 Trial assessments**

7.5.1 Descriptive and Inferential data analyses

Descriptive and inferential (where possible) analyses will be performed in IBM SPSS software (version 26) on health and intervention outcomes collected through survey and Mixpanel data. The survey will assess sociodemographic (e.g., diagnosis, age, gender, ethnicity, educational status, digital literacy) variables, health outcomes and will ask for expectations regarding the platform beforehand and satisfaction afterwards. Participants will be compared on health outcomes before and after the use of the platform to see if there are differences in health outcomes (e.g. weight, length, HbA1c, blood pressure, waist, generic health status, smoking yes/no) over time. Descriptive data of session frequency, session duration, pages visited, health score for recipes used on the platform as derived from Mixpanel will also be requested from platform developer to get insight into platform usage and support the selection of case studies. For Diabetes UK this will focus on traffic to site and referrals. Sub-group (or moderator analyses) according to expectations, age, ethnicity, diagnosis, digital literacy and sex will be conducted to examine possible differences in intervention and health outcomes. Data will be analysed using IBM SPSS Software, generating descriptive and inferential statistics with reported effect size, if data availability/quality allows.

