**Diabetes Related Health Status**

1. We would like to know your height. Would you like to answer in imperial (feet, inches) or metric (metres, centimetres) units? Please specify date DD/MM/YYYY.

□ Imperial (feet, inches)

□ Metric (metres, centimetres)

[Based on answer skip to drop down menus to select height in preferred units]

1. **How was this height measured:** (if other please specify)

□ Myself

□ Doctor

□ Other, please specify_________________________

□ Don’t know

□ Prefer not to say

1. We would like to know your weight. Would you like to answer in imperial (stones, pounds) or metric (kilograms) units? Please specify date DD/MM/YYYY.

□ Imperial (stones and pounds)

□ Metric (kilograms)

[Based on answer skip to drop down menus to select weight in preferred units]

1. **How was this weight measured:** (if other please specify)

□ Myself

□ Doctor

□ Other, please specify_________________________

□ Don’t know

□ Prefer not to say

1. We would like to know your waist size. Would you prefer to answer in imperial (inches) or metric units (centimetres)? Please specify date DD/MM/YYYY.

□ Imperial (inches)

□ Metric (centimetres)

[Based on answer skip to drop down menus to select waist size in preferred units]

[figure not shown]
Above the belly button, just below the rib cage. Bend to one side to find natural crease of your waist. Measure across at this point.

1. **How was this waist size measured:** (if other please specify)

□ Myself

□ Doctor

□ Other, please specify_________________________

□ Don’t know

□ Prefer not to say

1. What is your most recent blood glucose (sugar) level? (HbA1c mmol/mol)

□ Don’t know

□ Prefer not to say

1. What is the date of your most recent blood glucose level measurement?

DD/MM/YYYY

□ Don’t know

□ Prefer not to say

1. What is your most recent blood pressure level?

Systolic (top number) mmHg [drop down menu – 70, 80, 90, 100, 110, 120, 130, 140, 150, 160, 170, 180, 190]

Diastolic (bottom number) mmHg [drop down menu – 40, 50, 60, 70, 80, 90, 100]

□ Don’t know

□ Prefer not to say

1. What was the date of your most recent blood pressure level?

DD/MM/YY

□ Don’t know

□ Prefer not to say

1. What was your most recent HDL cholesterol level (mmol/L)?

[drop down menu]

□ Don’t know

□ Prefer not to say

1. What was your most recent TOTAL cholesterol level?

______________ mmol/L [drop down menu]

□ Don’t know

□ Prefer not to say

1. What is the date of your most recent cholesterol measurement?

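### The plan sets no date rule for the most-recent HbA1c and blood pressure values, so some 8-week changes may compare one test with itself; the HbA1c item is also worded as blood glucose

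*Combined protocol and SAP*

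**What the plan says.** Section 3.2 lists the health-status primary outcomes, among them "weight, BMI, HbA1c, blood pressure, waist, generic health status, smoking yes/no". On timing, section 7 says: "After 8 weeks of using the platform, participants will receive an invitation email" to the second survey.

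Under Diabetes Related Health Status, Attachment_4 (First Survey) and Attachment_6 (Second Survey) carry identical items:

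- HbA1c: "What is your most recent blood glucose (sugar) level? (HbA1c mmol/mol", followed by "What is the date of your most recent blood glucose level measurement".
- Blood pressure: "What is your most recent blood pressure level", followed by "What was the date of your most recent blood pressure level".
- Blood pressure values are picked from menus: "Diastolic (bottom number) mmHg [drop down menu – 40, 50, 60, 70, 80, 90, 100" for diastolic, and steps of 10 from 70 to 190 for systolic.

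Respondents may answer that they do not know, or decline, for both values and dates.

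On analysis, section 7.5.1 states: "Participants will be compared on health outcomes before and after the use of the platform to see if there are differences". Section 8.3.2 says much the same, and both add a general caveat about data availability and quality. Neither mentions the test dates. Section 8.6 is headed as dealing with missing or spurious data, but its text covers only interview recording and withdrawal. No procedure arranges an HbA1c or blood pressure measurement at either time point.

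**The concern.** A most-recent value asked for twice is a before/after pair only if a new test fell between the two surveys. Otherwise the second answer repeats a pre-platform result and the recorded change is zero by construction. Such pairs dilute the mean change toward zero. They also shrink the observed spread, so the confidence interval is too narrow around a diluted estimate. A platform that works could then appear not to, and the results are meant to inform a business case and further roll-out.

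The HbA1c item adds a separate problem. It names one quantity and gives the unit of another, and its date question mentions only blood glucose. A respondent with a home meter could enter a glucose reading, or could attach a recent glucose date to an old HbA1c. The second error would make a stale value look fresh.

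**Working it through.** **Plan's own figure.** There is none to reproduce. Section 8.1 anticipates 200-300 survey participants and says the number was not derived statistically; no alpha, power, effect size or SD is given. What follows is illustration, using two-sided 5% and, for detectable differences, 80% power.

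**Step 1: repeated tests.**

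- From the documents: 8 weeks between surveys; n = 200-300.
- Assumed: routine tests at a regular interval of T weeks, randomly timed relative to the surveys; everyone completes both surveys and reports a value.
- Share with a new test: f = min(1, 8/T). Share repeating one test: 1 - f.
- Observed mean change = f × true change.
- Observed SD of change ≈ √f × true SD, so a paired test carries the information of about n × f pairs.
- Power for a true change of 0.2 SD = Φ(0.2√(nf) - 1.96).
- Detectable standardised change = (1.96 + 0.84)/√(nf).

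| Assumed T | New test, f | Same test twice | Fresh pairs (n = 200-300) | Power for 0.2 SD | Detectable change (SD) |
| --- | --- | --- | --- | --- | --- |
| 8 weeks or less | 100% | 0% | 200-300 | 81-93% | 0.20-0.16 |
| 13 weeks | 8/13 = 62% | 38% | 123-185 | 60-78% | 0.25-0.21 |
| 16 weeks | 8/16 = 50% | 50% | 100-150 | 52-69% | 0.28-0.23 |
| 26 weeks | 8/26 = 31% | 69% | 62-92 | 35-49% | 0.36-0.29 |
| 52 weeks | 8/52 = 15% | 85% | 31-46 | 20-27% | 0.51-0.41 |

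For example, an assumed true change of -4 mmol/mol would appear as about -2.5, -1.2 or -0.6 at T = 13, 26 or 52 weeks. At T = 26, the interval would be about √0.31 = 0.55 times the width that the same number of fresh pairs would give. Where T is at least 8 weeks, a new test falls on average 8/2 = 4 weeks into the window, so even fresh pairs reflect about half the intended exposure.

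These intervals illustrate HbA1c. Nothing restricts blood pressure to clinic readings, so home measurement could make staleness small there. The survey does not ask how blood pressure was measured, as it does for height, weight and waist, so the source cannot be told apart afterwards.

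**Step 2: the HbA1c label.** The value question is worded as blood glucose with an HbA1c unit in brackets; the date question drops HbA1c altogether. No range check is described. As a worst-case illustration, suppose 5% of respondents enter a glucose near 8 instead of an HbA1c near 58 at one survey only. The mean then moves by 0.05 × (58 - 8) = 2.5 mmol/mol. If the same people misread the item both times, most of that cancels from the change. The 5% is an assumption.

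**Step 3: the blood pressure menus.** Rounding to 10 mmHg adds variance 10²/12 to each reading, hence 2 × 100/12 = 16.7 mmHg² to a change. Variance inflation is 1 + 16.7/SD², and the effective sample lost is 1 - 1/inflation.

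| Assumed SD of change (mmHg) | Variance inflation | Effective sample lost |
| --- | --- | --- |
| 8 | 1.26 | 21% |
| 10 | 1.17 | 14% |
| 15 | 1.07 | 7% |
| 20 | 1.04 | 4% |

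A simulation of systolic pressure (assumed mean 135, SD 16) returned mean changes of -2.00 to -2.05 for a true -2, and -5.00 to -5.02 for a true -5. The grid therefore adds essentially no bias. For diastolic pressure (assumed mean 80, SD 10), with entries stopped at 100, a true -2 came out as -2.1 to -3.4 over the same SDs. Follow-up values in that simulation are more spread out than baseline values, so it shows that the cap can distort change, not how much it would here.

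**The case against.** The best defence is that the test dates are collected for both measures in both surveys, so an analyst could identify repeated or pre-platform values wherever the date is known. The analysis is conditional on data quality, the project is exploratory with no hypotheses, and these are two of many listed outcomes. The extracted HbA1c item shows no response field, so one cannot tell whether the software would reject a value in another unit, and the printed unit is the right one for HbA1c.

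Much of this limits the point, and three stronger readings should be set aside:

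- A reader might infer that the plan intends to compare values whatever their dates. It does not say so; it requests the dates and is silent on their use. The gap is a missing rule, not missing data.
- A reader might infer that most pairs are stale or misrecorded. A stale majority requires 1 - 8/T above one half, that is T above 16 weeks. The documents give neither a testing interval nor a misreporting rate.
- A reader might infer that the 10 mmHg grid hides change, since many people record zero, or that 26% variance inflation means 26% of the sample lost. Those who cross a step record 10 mmHg, so the mean is preserved, and the corresponding loss is 1 - 1/1.26 = 21%.

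What remains is that a general caveat about quality is not a rule. Without one, the pairs to keep would either not be selected at all or be selected after the results are seen. The glucose wording also weakens the dates on which any later repair would depend.

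**Conclusion.** The concern holds in a bounded form. As written, the same pre-platform test can serve as both before and after for two listed primary outcomes, and nothing in the analysis sections prevents it. The error pulls the estimated change toward zero. Its size is unknown: about 38% to 85% of HbA1c pairs under assumed intervals of 13 to 52 weeks, none if everyone is tested at least every 8 weeks, and possibly little for blood pressure. The HbA1c wording is a clear defect of the instrument, with an effect the documents do not allow one to quantify. The blood pressure grid is secondary: about 4-21% of the effective sample for an assumed SD of change from 20 down to 8 mmHg, with essentially no mean bias. The fixed upper ends (190 and 100) can distort change in people beyond them. The missing date rule and the wording are certain; the magnitudes rest on assumptions.

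**What to change.** **Date rule in section 8.3.2.** Analyse an HbA1c or blood pressure pair only if the before test is dated on or before the first survey and within a prespecified maximum age, and the after test is dated later than the first survey. Treat other or undated after values as missing. Report the number of valid pairs and the days from first survey to the after test.

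The first-survey date is the workable anchor. Under sections 7 and 8.5 people may withhold Mixpanel data, and neither survey asks when they first used the platform. Where usage data are shared, the first-use date can refine the rule, because the first survey is sent after sign-up and some before tests could postdate first use.

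**Survey items, both surveys.** Reword to *most recent HbA1c (long-term blood sugar test)* and *date of that HbA1c test*, with a choice of mmol/mol or % and a range check. Replace the blood pressure menus with numeric entry to 1 mmHg and no cap.

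**Cost.** A few edits to an online form and a short addition to 8.3.2, using dates already requested. The item changes should precede the first survey, so that both time points share one wording. The real price is fewer pairs, for example 62-92 of 200-300 if tests were 26 weeks apart. The rule removes the dilution but does not restore the lost power, and people who happen to be retested may differ from the rest, which is why the count of valid pairs must be reported.

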**Confidence regarding diabetes management and meal planning**

1. The platform made me feel more confident in managing my diabetes

| 1 – Very strongly disagree | 2 | 3 | 4 | 5 – Neither agree nor disagree | 6 | 7 | 8 | 9 | 10 – Very strongly agree |
| --- | --- | --- | --- | --- | --- | --- | --- | --- | --- |
|  |  |  |  |  |  |  |  |  |  |

1. After using the platform, I felt more confident in making healthy food choices

| 1 – Very strongly disagree | 2 | 3 | 4 | 5 – Neither agree nor disagree | 6 | 7 | 8 | 9 | 10 – Very strongly agree |
| --- | --- | --- | --- | --- | --- | --- | --- | --- | --- |
|  |  |  |  |  |  |  |  |  |  |

1. After using the platform, I feel more confident planning meals

| 1 – Very unconfident | 2 | 3 | 4 | 5 – Neither confident nor unconfident | 6 | 7 | 8 | 9 | 10 – Very confident |
| --- | --- | --- | --- | --- | --- | --- | --- | --- | --- |
|  |  |  |  |  |  |  |  |  |  |

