1.4 Treatment / Intervention (if applicable)

The sample consists of people with Type 1 or Type 2 Diabetes or those who are at risk of developing Type 2 Diabetes. People will be compared on health and intervention outcomes before and after using the platform to see if there are differences in outcomes over time. This will allow to make within group comparisons using descriptive and inferential (where possible) statistics.

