8.3.2 Primary outcome analysis

Participants will be analysed on health outcomes before and after they used the platform to see if there is an improvement within this group over time. These data will be analysed using IBM SPSS software (version 26) generating descriptive and inferential statistics with reported effect size (if data availability/quality allows). Descriptive data of platform usage (e.g. session frequency, session duration, pages visited, health score for recipes used) will also be provided by the platform developer through Mix panel. These data will be exported into IBM SPSS software (version 26) and will be used to select participants with different engagement levels (low vs. high) for participation in case studies and semi-structured interviews. Where possible descriptive data of platform usage will be related to health outcomes. Results of the case study interviews and semi-structured interviews will be transcribed verbatim and thematically analysed (based on Grounded Theory) resulting in overall key themes. Survey results will be exported to and coded using IBM SPSS software (version 26) and described using descriptive statistics (e.g. frequencies, percentages, medians and means) according to sociodemographic characteristics (e.g. ethnic group, age, digital literacy, educational level, diagnosis and sex).

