**Confidence regarding diabetes management and meal planning**

1. How confident do you currently feel in managing your diabetes?

| 1 – Very unconfident | 2 | 3 | 4 | 5 – Neither confident nor unconfident | 6 | 7 | 8 | 9 | 10 – Very confident |
| --- | --- | --- | --- | --- | --- | --- | --- | --- | --- |
|  |  |  |  |  |  |  |  |  |  |

1. How confident do you currently feel in making healthy food choices?

| 1 – Very unconfident | 2 | 3 | 4 | 5 – Neither confident nor unconfident | 6 | 7 | 8 | 9 | 10 – Very confident |
| --- | --- | --- | --- | --- | --- | --- | --- | --- | --- |
|  |  |  |  |  |  |  |  |  |  |

1. How confident do you currently feel in planning meals efficiently?

| 1 – Very unconfident | 2 | 3 | 4 | 5 – Neither confident nor unconfident | 6 | 7 | 8 | 9 | 10 – Very confident |
| --- | --- | --- | --- | --- | --- | --- | --- | --- | --- |
|  |  |  |  |  |  |  |  |  |  |

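### Confidence, a listed primary outcome, is asked as a current level before and as perceived change after, so it cannot be compared as paired levels

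*Combined protocol and SAP*

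**What the plan says.** Section 3.2 puts "confidence in diabetes management and meal planning, healthy eating" among its examples of primary outcomes on health status and condition management. Section 1.4 gives the design: "People will be compared on health and intervention outcomes before and after using the platform". Section 8.3.2 gives the primary analysis: "Participants will be analysed on health outcomes before and after they used the platform to see if there is an improvement". It names no test and no change score.

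The first survey (Attachment 4) has three confidence items. All ask for the current level: "How confident do you currently feel in managing your diabetes", "How confident do you currently feel in making healthy food choices", and a parallel question on planning meals efficiently. All three run from 1 (very unconfident) through 5 (neither) to 10 (very confident).

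The second survey (Attachment 6) has three items under the same block heading. Item 1 is "The platform made me feel more confident in managing my diabetes". Item 2 is a similar statement about healthy food choices, introduced as applying after platform use. Both run from 1 (very strongly disagree) to 10 (very strongly agree). Item 3 is "After using the platform, I feel more confident planning meals", answered on the confident/unconfident anchors of the first survey.

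**The concern.** A before/after comparison needs the same quantity measured twice. Here the first survey records a level and the second records an opinion about change. The two blocks share a heading and 1-to-10 numbering, and no scoring rule says how they relate, so it would be easy to subtract one from the other and report the result as change in confidence. The results are meant to inform a decision on a business case (sections 1 and 2). If the second survey goes out as written, the follow-up level of confidence is never collected, and no later analysis can recover it.

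**Working it through.** The documents give no figure to reproduce for this outcome: no effect size, standard deviation or error rate. The check is an item-by-item comparison, followed by a short calculation of what a difference score would measure.

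**Step 1. Pair the items (Attachment 4 against Attachment 6).**

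| Item | First survey | Second survey | Same question? | Same anchors? |
| --- | --- | --- | --- | --- |
| 1. Diabetes management | Current level | Agreement that the platform raised confidence | No | No |
| 2. Food choices | Current level | Agreement that confidence was higher after use | No | No |
| 3. Meal planning | Current level, planning efficiently | Change-worded statement, efficiency not mentioned | No | Yes |

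**Step 2. Look for the level elsewhere at follow-up.** The Satisfaction block of the second survey asks whether the platform gave support, not how confident the respondent now is. The case study outline (Attachment 10) raises confidence only as an open question. Nothing repeats the current-level items.

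**Step 3. Compare with the other health outcomes.** The 0-100 health rating, height, weight, waist, HbA1c, blood pressure, smoking and the eight healthy-eating items are asked in the same way in both surveys. Among the health outcomes named in section 3.2, only confidence was reworded.

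**Step 4. What a difference would measure, items 1 and 2 only.** Assumption: a respondent whose confidence has not changed answers 5, the labelled neutral point of the agreement scale. Then

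after - before = 5 - baseline

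- baseline 1: 5 - 1 = +4
- baseline 3: 5 - 3 = +2
- baseline 5: 5 - 5 = 0
- baseline 8: 5 - 8 = -3
- baseline 10: 5 - 10 = -5

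With no true change, the difference runs from -5 to +4 and depends only on the baseline level. For an assumed mean baseline of 6 to 8, the mean difference is 5 - 6 = -1 to 5 - 8 = -3.

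The sign can also reverse. Suppose true confidence rises from 9 to 10 and the respondent answers 7 for agreement. The difference is 7 - 9 = -2, while the true change is 10 - 9 = +1.

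Because the error follows baseline, it would carry into the subgroup comparisons of section 8.4. Two groups with assumed mean baselines of 5 and 8 and no change in either would show 0 and -3, a spurious gap of 3 points.

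**Step 5. Item 3.** The calculation in step 4 does not carry over, because item 3 has no agree/disagree midpoint. A respondent who follows the printed anchors reports a level, and an unchanged respondent at 8 gives 8 - 8 = 0. A respondent who follows the statement and uses 5 for no change gives 5 - 8 = -3. The data cannot show which reading was used.

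**The case against.** The strongest reply is that the plan never commits to subtracting these scores. Section 8.3.2 names no change score and makes inferential statistics conditional on data availability and quality. It also plans to describe survey answers by frequencies, percentages, medians and means, which suits the second-survey items. The before/after examples in section 7.5.1 leave confidence out. The project has no hypotheses, its sample size is not statistically derived, and confidence is one of about ten example health outcomes.

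Much of this limits the point. A reader might infer that the plan sets out an invalid calculation. It does not; the defect is a missing paired measure. A reader might also infer that confidence cannot be evaluated at all. That goes too far: the second survey still yields retrospective perceived change, and the case studies ask about confidence. Nor are all three items on changed scales, since item 3 keeps its anchors. Only item 1 explicitly credits the platform; items 2 and 3 refer to the time after use. The food-choices item is not named in section 3.2, although that list is given as examples.

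The reply does not remove the defect. The list in section 7.5.1 is also one of examples, and sections 1.4 and 3.2 together bring confidence into the before/after aim. An exploratory purpose explains the lack of a power calculation, but it does not supply a follow-up measurement. Describing perceived change is legitimate, but it is a different quantity from the one planned, and it leaves the first-survey items without a counterpart.

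**Conclusion.** The point holds for all three items: confidence cannot be compared as paired levels, and only perceived change can be described. This conclusion rests on the survey wording alone and needs no assumption.

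The numbers are an illustration for items 1 and 2, resting on two assumptions: that an unchanged respondent answers 5, and that mean baseline confidence is 6 to 8. Under these, no change would look like a fall of 1 to 3 points. A reader might take that range as an estimate of bias, but the documents do not support this. They give no baseline distribution, and someone with unchanged confidence could reasonably disagree with a statement of increased confidence and answer below 5.

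The correction should be made before the second survey is sent, because the loss is permanent afterwards.

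**What to change.** Repeat the three confidence items of Attachment 4 in Attachment 6, word for word and with the same 1-10 anchors. Add one sentence to section 8.3.2 stating that before/after change in confidence is computed only from these pairs.

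Keep the existing second-survey statements as separate perceived-benefit items, give all three the agree/disagree anchors, and report them descriptively. Where they sit in the questionnaire does not matter.

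The cost is three extra online items, under a minute per respondent, one changed set of anchors and one sentence in the analysis plan.
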